## **2.9 BLINDING AND UNBLINDING**

No procedures for treatment masking have been used in the study, however the present SAP has been written by a statistician blinded to treatment allocations and study results.

## **3 POPULATIONS OF ANALYSIS**

The populations of analysis were not originally identified in the study protocol.

The primary and secondary efficacy analyses will be performed on the intention-to-treat (ITT) population. The same evaluations will be repeated on the per-protocol population, as sensitivity analyses.

The safety analyses will be performed on the safety population.

### **3.1 RANDOMIZED POPULATION**

The randomized population will include all randomized preterm infants. Patients will be reported under their randomized intervention arm.

### **3.2 INTENTION-TO-TREAT POPULATION**

The intention-to-treat population will include all randomized preterm infants. Patients erroneously registered twice or more into the study will be accounted for only once. Patients will be analysed according to the treatment assigned at the end of the randomization procedure. For patients registered twice or more the first assigned treatment should be taken as reference.

### 3.3 PER-PROTOCOL POPULATION

The per-protocol population will include all randomized preterm infants with no violation of eligibility criteria and interventional protocol. Preterm infants non-assisted with the procedure assigned by the minimization algorithm will be excluded from the per-protocol population.

### 3.4 SAFETY POPULATION

The safety population will include all randomized preterm infants who have received assistance according to one of the two interventional protocol procedures. Patients will be analysed according to type of assistance they received.

### 3.5 TREATMENT MISALLOCATIONS

If a preterm infant was:

- randomized but was assisted with the alternative study procedure, then he/she will be anyway reported under his/her randomized interventional group for primary and secondary efficacy analyses but will be reported under the treatment he/she received for all safety analyses.
- randomized but was assisted with an off-protocol procedure, then he/she will be reported under his randomized interventional group for all primary and secondary efficacy analyses and will be excluded from the safety analyses.
- preterm infants in which a treatment misallocation occurred, by definition, will not be included in the per-protocol analyses.

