### 182 **Study Procedures**

183 Patients are randomly allocated to one of the following treatment groups:

184 – Group I: patients are assisted with the PCI while lying supine on a portable resuscitation trolley  
185 (Lifestart trolley™, Inspiration Healthcare, UK) and the cord is clamped at the end of the 3rd min  
186 of life. In case the treatment is not performed due to maternal or neonatal reasons the infant will  
187 receive an immediate cord clamping.

188 – Group II: patients receive cord UCM without placental refill (milking four times 20 cm of cord at  
189 a speed of about 10 cm/sec) and then clamped before 20 sec of life. In case the treatment is not

190 performed due to maternal or neonatal reasons the infant will receive an immediate cord  
191 clamping.

192 Compliance will be defined as full adherence to the protocol. Compliance with the protocol will be  
193 ensured by a number of procedures included in the site set-up. The local principal investigator  
194 participated in preparatory meetings in which details of the study protocol and data collection were  
195 accurately discussed. All centers received detailed instruction on study procedures and web-based  
196 recording data.

197 All infants will be resuscitated following the current guidelines of the American Academy of  
198 Pediatrics (AAP) (15). Neonatal care will be started with  $\text{FiO}_2$  of 0.30 in both the groups, in  
199 agreement with local protocols. Respiratory support in the delivery room will be given using a T-  
200 piece ventilator (Neopuff Infant T-Piece Resuscitator, Fisher & Paykel, Auckland, New Zealand),  
201 which is a pressure-limited mechanical device that supplies consistent peak inspiratory pressure  
202 (PIP) and positive end expiratory pressure (PEEP), and can deliver sustained inflation (16). Initial  
203 PIP and PEEP values will be set at 20 and 5  $\text{cmH}_2\text{O}$  respectively. To avoid pressure leakage, a  
204 neonatal mask of appropriate size, which adequately covers both the mouth and nostrils of  
205 infants, will be used. The flow rate will be set at 10 L/min without changes during the  
206 resuscitation. Spontaneously breathing babies with a respiratory effort present or with a  
207 suboptimal  $\text{SpO}_2$  on pulse oximeter will be assisted in nCPAP. In the delivery room, infants will be  
208 started on mechanical ventilation (MV) if they have not reached the goal of 70%  $\text{SpO}_2$  by 5  

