## 2.6 INTERVENTIONAL GROUPS

Preterm infants were randomly allocated to one of the two interventional arms reported in Table 1.

**Table 1:** The two interventional arms of the study.

| Arm      | Intervention                                                                                                                                   |
|----------|------------------------------------------------------------------------------------------------------------------------------------------------|
| A | Control: assistance on the neonatal resuscitation table, after performing cord milking followed by umbilical cord clamping              |
| B | Experimental: assistance with intact placental circulation, keeping the newborn near the mother's bed at the same level as the placenta |

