## 4.2 SAFETY VARIABLES

Safety of the study interventional procedures will be evaluated by the following variables:

Intubation in delivery room  
Compressions in delivery room  
Use of i.v. adrenaline in delivery room  
Use of ET adrenaline in delivery room  
Use of surfactant in delivery room  
Total number of surfactant doses  
CRIB II score  
Max serum bilirubin  
Exchange transfusions  
Need of mechanical ventilation in the first 24 hours  
Duration of mechanical ventilation in the first 24 hours (hrs)  
Pharmacological closure of PDA  
Incidence of NEC  
Incidence of PLV  
Incidence of IVH  
Incidence of ROP  
Incidence of sepsis

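### Infants given the protocol's fallback of immediate clamping appear in no planned safety table, so 16 of the 17 safety variables are never compared in all randomised infants

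*Combined protocol and SAP*

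**What the plan says.** Protocol, Study Procedures, sets the same fallback for both groups. For the intact-cord group the text reads "In case the treatment is not performed due to maternal or neonatal reasons the infant will" and goes on to immediate clamping. For the milking group the corresponding words are "performed due to maternal or neonatal reasons the infant will receive an immediate cord" clamping.

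SAP 2.6 defines two arms only. The control is "assistance on the neonatal resuscitation table, after performing cord milking followed by umbilical cord clamping". The experimental arm is assistance at the mother's bedside with the placental circulation intact. Immediate clamping without milking is neither.

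SAP 3.4 defines the safety population as "all randomized preterm infants who have received assistance according to one of the two interventional protocol procedures", and adds: "Patients will be analysed according to type of assistance they received". SAP 3.5 keeps infants who had an off-protocol procedure in their randomised arm for efficacy, "and will be excluded from the safety analyses". SAP 5.2.4 reports safety in the safety and per-protocol populations only. SAP 3.3 and 3.5 remove from the per-protocol set any infant not assisted with the assigned procedure.

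SAP 4.2 lists 17 safety variables, beginning with "Intubation in delivery room". They are displayed in Appendix 1, Tables 6.1 to 6.17, each with columns for Arm A and Arm B only.

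**The concern.** Membership of the safety set depends on something that happens after randomisation. The protocol ties that event to maternal or neonatal reasons, and the outcomes include resuscitation measures in the same minutes and ventilation in the hours that follow. If fallback is more frequent in one arm, or the infants who need it differ in risk between arms, the as-treated contrast is no longer protected by randomisation.

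One affected variable is more than a safety check. Need for mechanical ventilation in the first 24 hours heads the protocol's list of other secondary data (Secondary Outcomes) and is the first short-term benefit named in SAP 2.2. The SAP analyses it only as a safety variable (4.2, Table 6.10). A benefit claimed for the experimental arm would thus be tested only in sets from which the fallback infants have been removed.

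**Working it through.** **Tracing one infant.** Take an infant randomised to either arm whose procedure is not performed and who is clamped immediately.

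- ITT (SAP 3.2, 3.5): included, in the assigned arm.
- Safety population (SAP 3.4, 3.5): not included, because neither SAP 2.6 procedure was given.
- Per-protocol (SAP 3.3, 3.5): not included.
- Appendix 1: counted in the Other row of Table 1.6 and listed in Tables 1.5, 1.7 and 1.8. No safety outcome is tabulated by arm.

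**What ITT still covers** (SAP 4.1, 5.2.2, 5.2.3): death, grade 3-4 and any IVH, moderate or severe BPD, Apgar, overall invasive ventilation, dopamine and dobutamine, and transfusions, among others.

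**What it does not.** Of the 17 variables in SAP 4.2, only IVH is also analysed in ITT. The other 16 are delivery-room intubation, compressions, intravenous and endotracheal adrenaline, and surfactant; total surfactant doses; CRIB II; maximum bilirubin; exchange transfusion; need for and duration of ventilation in the first 24 hours; pharmacological PDA closure; NEC; periventricular leukomalacia; ROP; and sepsis.

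**Size.** The plan states no fallback rate, so there is no figure to reproduce. Everything below is assumption.

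*Illustration 1: no true effect, same overall risk in both arms.* Let f_p and f_u be the fallback proportions in the intact-cord and milking arms, h the intubation risk in fallback infants, and 0.30 the risk in the remaining intact-cord infants.

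- Overall risk in either arm = f_p × h + (1 − f_p) × 0.30
- Safety-set risk, intact cord = 0.30
- Safety-set risk, milking = (overall − f_u × h) / (1 − f_u)

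| f_p | f_u | h | Overall | Milking safety set | Spurious gap (points) |
|---|---|---|---|---|---|
| 0.05 | 0.05 | 0.60 | 0.315 | (0.315 − 0.030)/0.95 = 0.300 | 0 |
| any | any | 0.30 | 0.300 | 0.300 | 0 |
| 0.10 | 0.05 | 0.60 | 0.330 | (0.330 − 0.030)/0.95 = 0.316 | 1.6 |
| 0.20 | 0.05 | 0.60 | 0.360 | (0.360 − 0.030)/0.95 = 0.347 | 4.7 |
| 0.20 | 0.05 | 0.80 | 0.400 | (0.400 − 0.040)/0.95 = 0.379 | 7.9 |
| 0.30 | 0.02 | 0.80 | 0.450 | (0.450 − 0.016)/0.98 = 0.443 | 14.3 |

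Over f_p 0.10-0.30, f_u 0.02-0.05 and h 0.60-0.80, the gap runs from 1.6 to 14.3 points in favour of intact cord. It is zero when fallback is equally frequent in both arms or carries no extra risk. It changes sign if fallback is commoner under milking.

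*Illustration 2: a real as-randomised excess.* Assume a risk of 0.20 in infants given their procedure in both arms, 0.30 to 0.60 in fallback infants, f_p 0.05 to 0.30 and f_u 0.05. The as-randomised difference is (f_p − f_u) × (fallback risk − 0.20). This runs from 0 (f_p = 0.05) to 0.25 × 0.40 = 0.10. The planned safety set shows 0 throughout.

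With the protocol's 106 per group, the rule drops 106 × 0.05 ≈ 5 to 106 × 0.30 ≈ 32 intact-cord infants and about 5 milking infants. The dropped infants carry between 0.05 × 0.30/0.205 = 7% and 0.30 × 0.60/0.32 = 56% of the intact-cord arm's events, against 7% to 14% in the milking arm.

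**The case against.** The SAP never names immediate clamping as off-protocol, and the protocol itself prescribes it. One could call this an undefined term and not a decision to exclude. That affects the wording of the criticism but not the result: the inclusion rule in SAP 3.4 leaves these infants out by itself.

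A reader might infer that harm from attempting bedside care and then having to clamp early would be invisible. The documents do not support this. The fallback applies when the procedure is not performed. An infant whose intact-cord period was started and cut short is a different case. SAP 2.6 sets no minimum duration, so that infant may well stay in the safety set under Arm B. The SAP does not say. Death, IVH, BPD, Apgar and overall invasive ventilation also stay in ITT and could register such harm.

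A reader might also infer that serious adverse events are reviewed only in the reduced set. Protocol, Data Safety and Monitoring Board, contains no such limit: the board reviews all deaths and adverse effects, and the interim look covers the first 100 infants enrolled. Tables 1.5 and 1.6 would also show any imbalance in exclusions, although not its effect on outcomes.

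Direction is uncertain. Fallback may have purely maternal causes. The one obstacle that the SAP describes, a short cord not identifiable before randomisation (2.5.2), might hinder either procedure. Support for more fallback in the intact-cord arm is indirect: 3 minutes against under 20 seconds, and a requirement to record failures (Allocation concealment) and an adherence concern (Discussion) stated for that arm only.

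Reporting safety as treated, with crossovers moved to the procedure received, is a common convention and is openly stated. It is not the fault here. The fault is that no as-randomised analysis stands beside it and that one group is dropped altogether.

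**Conclusion.** The concern holds within limits. Infants who receive the fallback and neither study procedure are in no planned safety table, and 16 safety variables, including a protocol secondary outcome, have no all-randomised analysis. This follows from the population rules and needs no assumption.

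The bias itself does depend on assumptions. It arises if the frequency of fallback, or the risk of the infants who receive it, differs between arms. A lean in favour of the intact-cord arm is plausible but not shown. The size is about 0 points if fallback is similar in both arms or unrelated to risk, and 1.6 to 14.3 points under the illustrated ranges. Even with equal fallback, events are undercounted in both arms when fallback infants are at higher risk.

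The primary analysis and its components are unaffected. This should be fixed, but it does not undermine the trial's main conclusion.

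**What to change.** - In SAP 3.4, 3.5 and 5.2.4, analyse the SAP 4.2 variables in all randomised infants by assigned arm, counting fallback immediate clamping as part of the assigned strategy.
- Keep the as-treated tables as supportive, with a separate column for other procedures or immediate clamping in place of exclusion.
- Define off-protocol procedure, and state how a started but shortened intact-cord period is classified for the safety and per-protocol sets.

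The cost is some SAP wording and one extra set of tables. No new data are needed: Table 1.6 already requires the procedure received, and the efficacy analyses already keep these infants in their assigned arm.

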### 3.6 PROTOCOL DEVIATIONS

The full list of protocol deviations to be included in the study report, those assessed either prior to randomization or after randomization, will be compiled prior to database closure, following the blinded evaluation of the study coordinator.

## 4 ENDPOINTS AND COVARIATES

### 4.1 EFFICACY VARIABLES

#### 4.1.1 Primary efficacy variable

The primary efficacy variable is a composite endpoint that consists of grade 3-4 IVH, moderate/severe BPD, and death at 36 weeks of post-conceptional age.

IVH and BPD were diagnosed following the criteria of Papile (19) and Jobe and Bancalari (20), respectively.

#### 4.1.2 Secondary efficacy variables

The secondary efficacy variables are:

- The single components of the composite endpoint
- The variables reported in list below:
  - 1 min Apgar score
  - 5 mins Apgar score
  - FiO2 max in delivery room
  - Use of neopuff
  - Use of physiological solution
  - Use of sodium bicarbonate
  - Body temperature (°C) at intensive care admission
  - Surgical treatment for patent ductus arteriosus (PDA)
  - Incidence of IVH
  - Use of non-invasive mechanical ventilation
  - Duration of non-invasive mechanical ventilation (days)
  - Use of invasive mechanical ventilation
  - Duration of invasive mechanical ventilation (days)
  - iNO administration
  - Duration of iNO administration (days)
  - Need of erythrocyte concentrate transfusions
  - Number of erythrocytes concentrate transfusions
  - Use of oxygen therapy
  - Duration of oxygen therapy (days)
  - FiO2 max during oxygen therapy (%)
  - Dopamine use in the first 24 hours
  - Dobutamine use in the first 24 hours
  - Overall duration of hospitalization (days)
  - 3-hour cerebral oxygenation
  - 6-hour cerebral oxygenation
  - 12-hour cerebral oxygenation
  - 18-hour cerebral oxygenation
  - 24-hour cerebral oxygenation
  - Superior vena cava blood flow in the first 24 hours (ml/Kg/min)
  - PAP value (mmHg)
  - Right ventricular ejection (ml/Kg/min)
  - Left ventricular ejection (ml/Kg/min)
  - Presence of transductal shunt
  - Hb max (g/dl) in the first 24 hours
  - Ht max (%) in the first 24 hours
  - 3-hour average PAS (mmHg)
  - 6-hour average PAS (mmHg)
  - 12-hour average PAS (mmHg)
  - 18-hour average PAS (mmHg)
  - 24-hour average PAS (mmHg)

S/D AMS  
PI AMS  
RI AMS  
AMS diastolic flow  
S/D ACA  
PI ACA  
RI ACA  
ACA diastolic flow

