### 130 **Further collected data**

131 The following data will be recorded for each infant: gestational age; birth weight; sex; mode of  
132 delivery; Apgar score at 1 and 5 min; main maternal pathologies; antenatal steroid treatment;  
133 maternal analgesia/anesthesia; highest FiO2 in the delivery room; need for resuscitation  
134 procedures at birth (positive pressure ventilation, intubation, chest compressions, drugs); body  
135 temperature at admission; hemoglobin and hematocrit maximum values in the first 24 hours; the  
136 highest FiO2 and mean airway pressure (MAP) values; need and duration of non-invasive  
137 (NCPAP, biphasic positive airway pressure, nasal intermittent mandatory ventilation), and  
138 invasive (patient-triggered ventilation or high frequency oscillatory ventilation) respiratory support;  
139 and need and duration of nitric oxide therapy. We will also report the occurrence of patent ductus  
140 arteriosus (PDA) requiring pharmacological or surgical treatment, of IVH, periventricular  
141 leukomalacia (PVL), NEC, ROP, and hospital stay duration.

142 A diagnosis of sepsis will be based on clinical and laboratory data (white cell count, C-reactive  
143 protein concentration) and will be confirmed by positive blood cultures (9). IVH will be graded  
144 according to a standard classification system (10). A diagnosis of PVL will be made when cystic  
145 areas are detected by cerebral ultrasonography at 40 weeks post-conception birth (11). BDP will  
146 be diagnosed according to the definition by Jobe and Bancalari (12). ROP will be graded  
147 according to the international classification of retinopathy of prematurity (13). NEC will be  
148 diagnosed in agreement with classical Bell's criteria (14).

149

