## 4.3 HANDLING OF MISSING VALUES

Generally, subjects with missing value for a particular endpoint will contribute to the specific patient population and will be reported in all analyses as a special category ("missing value").

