### 5.2.3 Secondary efficacy analyses

Data regarding the secondary efficacy variables will be presented by treatment group and will be reported for the ITT and PP populations. Evaluations on the PP population would be considered as sensitivity analyses.

The statistical analysis of the single components of the composite endpoint will be conducted with the same approach adopted for the primary efficacy variable.

The other secondary efficacy variables will be analysed according to their type.

Discrete variables will be summarized by frequencies and percentages. Percentages will be calculated according to the total number of patients assigned to each interventional group and to the total number of patients included in the specific analysis population. The proportions of events occurred in the two interventional arms will be compared with the chi-square test for heterogeneity or the Fisher's exact test, if appropriate.

Continuous variables will be summarized by use of standard measures of central tendency and dispersion: mean, standard deviation (SD), standard error (SE), median, minimum, maximum, interquartile range (IQR). The average values of each parameter observed in the two interventional arms will be compared by means of the Wilcoxon two-sample test.

No adjustment for multiplicity will be adopted.

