|                    | Treatment Arm |   |       |   | Total |   |
|--------------------|---------------|---|-------|---|-------|---|
|                    | Arm A         |   | Arm B |   |       |   |
|                    | N             | % | N     | % | N     | % |
| Blood transfusions |               |   |       |   |       |   |
| No                 |               |   |       |   |       |   |
| Yes                |               |   |       |   |       |   |
| Missing value      |               |   |       |   |       |   |
| Total              |               |   |       |   |       |   |

NOTE: Arm A = UMBELICAL CORD MILKING, Arm B = DELAYED UMBELICAL CORD CLAMPING

TABLE 5.18: NUMBER OF ERYTHROCYTE CONCENTRATE TRANSFUSION BY TREATMENT ARM (5)

*INTENTION-TO-TREAT POPULATION*

|                              |                | Treatment Arm |       | Total |
|------------------------------|----------------|---------------|-------|-------|
|                              |                | Arm A         | Arm B |       |
| Number of blood transfusions | N              |               |       |       |
|                              | Missing        |               |       |       |
|                              | Mean           |               |       |       |
|                              | SD             |               |       |       |
|                              | Median         |               |       |       |
|                              | Minimum        |               |       |       |
|                              | First quartile |               |       |       |
|                              | Third quartile |               |       |       |
|                              | Maximum        |               |       |       |

NOTE: Arm A = UMBELICAL CORD MILKING, Arm B = DELAYED UMBELICAL CORD CLAMPING

TABLE 5.19: DISTRIBUTION OF PATIENTS BY USE OF OXYGEN THERAPY AND TREATMENT ARM (1)

*INTENTION-TO-TREAT POPULATION*

|                | Treatment Arm |   |       |   | Total |   |
|----------------|---------------|---|-------|---|-------|---|
|                | Arm A         |   | Arm B |   |       |   |
|                | N             | % | N     | % | N     | % |
| Oxygen therapy |               |   |       |   |       |   |
| No             |               |   |       |   |       |   |
| Yes            |               |   |       |   |       |   |
| Missing value  |               |   |       |   |       |   |

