| Total          |               |   |       |   |       |   |

NOTE: Arm A = UMBELICAL CORD MILKING, Arm B = DELAYED UMBELICAL CORD CLAMPING

TABLE 5.20: DURATION OF OXYGEN THERAPY BY TREATMENT ARM (5)

*INTENTION-TO-TREAT POPULATION*

|                 |                | Treatment Arm |       | Total |
|-----------------|----------------|---------------|-------|-------|
|                 |                | Arm A         | Arm B |       |
| Duration (days) | N              |               |       |       |
|                 | Missing        |               |       |       |
|                 | Mean           |               |       |       |
|                 | SD             |               |       |       |
|                 | Median         |               |       |       |
|                 | Minimum        |               |       |       |
|                 | First quartile |               |       |       |
|                 | Third quartile |               |       |       |
|                 | Maximum        |               |       |       |

NOTE: Arm A = UMBELICAL CORD MILKING, Arm B = DELAYED UMBELICAL CORD CLAMPING

TABLE 5.21: FiO2 MAX DURING OXYGEN THERAPY BY TREATMENT ARM (5)

*INTENTION-TO-TREAT POPULATION*

|              |                | Treatment Arm |       | Total |
|--------------|----------------|---------------|-------|-------|
|              |                | Arm A         | Arm B |       |
| FiO2 max (%) | N              |               |       |       |
|              | Missing        |               |       |       |
|              | Mean           |               |       |       |
|              | SD             |               |       |       |
|              | Median         |               |       |       |
|              | Minimum        |               |       |       |
|              | First quartile |               |       |       |
|              | Third quartile |               |       |       |
|              | Maximum        |               |       |       |

NOTE: Arm A = UMBELICAL CORD MILKING, Arm B = DELAYED UMBELICAL CORD CLAMPING

TABLE 5.22: DISTRIBUTION OF PATIENTS BY DOPAMINE USE IN THE FIRST 24 HOURS AND TREATMENT ARM (1)  
*INTENTION-TO-TREAT POPULATION*

|               | Treatment Arm |   |       |   | Total |   |
|---------------|---------------|---|-------|---|-------|---|
|               | Arm A         |   | Arm B |   |       |   |
|               | N             | % | N     | % | N     | % |

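### As worded, the maximum-FiO2 comparison covers only infants given oxygen, a group selected after randomisation; the coding of infants never given oxygen must be stated

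*Combined protocol and SAP*

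**What the plan says.** SAP 4.1.2 includes both "Use of oxygen therapy" and "FiO2 max during oxygen therapy" among the secondary efficacy variables.

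- **Oxygen use** is displayed with No and Yes rows and tested between arms in "TABLE 5.19: DISTRIBUTION OF PATIENTS BY USE OF OXYGEN THERAPY AND TREATMENT ARM (1"). The plan therefore allows for infants who never receive oxygen, and for a difference between arms in how many there are.
- **Maximum FiO2** is displayed in "TABLE 5.21: FiO2 MAX DURING OXYGEN THERAPY BY TREATMENT ARM (5"), labelled intention-to-treat. Its rows are N, Missing and summary statistics, with none for infants not given oxygen. Footnote 5 of Appendix 1 is the Wilcoxon rank-sum output.
- **Test.** SAP 5.2.3 says of continuous variables: "The average values of each parameter observed in the two interventional arms will be compared by means of the Wilcoxon two-sample test".
- **Missing values.** SAP 4.3 says that "subjects with missing value for a particular endpoint will contribute to the specific patient population and will be reported in all analyses" under a missing-value category. It does not mention values that are not applicable.
- **Protocol.** The section on further collected data opens with "The following data will be recorded for each infant", and the list that follows includes the highest FiO2. The restriction to periods of oxygen therapy appears only in the SAP.

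**The concern.** Oxygen use is an outcome that the intervention may change. A variable that exists only for oxygen users conditions on that outcome, so the groups compared are no longer those that randomisation formed, whatever the table label says.

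The direction is awkward. Infants without a value are those with the least need. Suppose two infants in an arm would have peaked at 30% and 60%. If the intervention spares the first infant oxygen altogether, that arm's values go from {30, 60} to {60}, and a benefit is scored as a rise. At stake is whether this row of the results can be read as a randomised comparison, and in some circumstances whether it points the wrong way.

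**Working it through.** **Inputs from the documents.** SAP 2.7 gives 100 infants per arm and a two-sided 5% level. The plan states no figure for maximum FiO2, so the only design figure to reproduce is the sample size for the primary composite, 47% vs 28%:

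n = [1.96·√(2·0.375·0.625) + 0.842·√(0.47·0.53 + 0.28·0.72)]² / 0.19² ≈ 101 per arm, and 100 per arm gives 79.7% power. This matches the stated 100 and 80%. The present point does not touch it.

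**Assumed inputs.** The documents give neither the share of infants never given oxygen nor the distribution of peak FiO2. All FiO2 results below rest on assumptions.

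**Step 1: worked example.** Give both arms the same 100 peak values, evenly spaced from 22 to 80 (step 58/99). The mildest 10 control infants and the mildest 20 experimental infants receive no oxygen.

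- Users only, control: (22 + 10·58/99 + 80)/2 = 53.9
- Users only, experimental: (22 + 20·58/99 + 80)/2 = 56.9, Wilcoxon p = 0.21
- All infants with non-users at 21, control: 0.90·53.93 + 0.10·21 = 50.6
- All infants with non-users at 21, experimental: 0.80·56.86 + 0.20·21 = 49.7

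The sign reverses: +2.9 points among users, −0.9 points among all infants. With 5 vs 10 infants without oxygen the figures are 52.5 vs 53.9 among users (p = 0.54) and 50.9 vs 50.6 among all.

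**Step 2: simulation, 100 per arm, 2,000 trials per scenario.** Severity L is standard normal. An infant receives oxygen if L exceeds a threshold t set by the control use rate. Peak FiO2 is min(100, 25 + 20·(L − t)^1.3) for users. Two kinds of effect were tried:

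- *Spare*: the experimental arm has a higher threshold for oxygen, and nobody else's FiO2 changes.
- *Shift*: severity falls in every experimental infant by the amount that gives the same lower use rate.

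| Oxygen use, control vs experimental | Spare: users-only test significant against the better arm | Shift: power, users only | Shift: power, all infants, non-users at 21% |
|---|---|---|---|
| 98 vs 95% | about 6% | – | – |
| 95 vs 90% | about 9% | – | – |
| 90 vs 80% | about 25% | 61% | 84% |
| 80 vs 65% | 47 to 50% | 47% | 86% |
| 70 vs 50% | 77 to 78% | 41% | 92 to 93% |

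Ranges are results of repeated runs. The nominal rate for the first results column is 2.5%, one tail of the 5% test. Simulation error at 25% is about √(0.25·0.75/2000) = 1 percentage point. In the shift model, wrong-direction significance occurred in at most 0.05% of trials.

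**Step 3: a different distribution.** With peak FiO2 = 21 + gamma (shape 2, scale 10) and a sparing effect, wrong-direction significance is 4.8% (2 vs 5% without oxygen), 8.2% (5 vs 10%), 25% (10 vs 20%) and 67% (10 vs 30%). Scoring non-users as 21% gives 2.1%, 1.7%, 1.9% and 0.3%. With no difference in use (5 vs 5%), the users-only rate is 2.6%, as it should be.

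**The case against.** **The coding is inferred.** No sentence says that infants without oxygen go into the Missing row. SAP 4.3 speaks of missing values only, and the protocol records highest FiO2 for each infant, so the database may hold 21% for them. This stands. A reader might infer that the best infants are certain to be dropped; the documents support only that the variable, as worded, has no value for them and that no rule supplies one. The SAP does handle the matter elsewhere: Table 2.7 has a row for no oxytocin, separate from missing.

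**Reversal needs a particular effect and low oxygen use.** This also stands. Only the sparing model reverses the sign. These infants are below 30 weeks and delivery-room care starts at FiO2 0.30, so near-universal oxygen use is plausible and the bias would then be small. The rates of about 50% and 78% should not be taken as the expected size.

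**The variable is minor.** Maximum FiO2 is not among the protocol's secondary outcomes and is not named in the SAP 2.2 rationale, so a reader should not infer that the trial's hypothesis rests on it. It is one of 49 secondary tables (5.1 to 5.49), without multiplicity adjustment.

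**The plan lets a reader notice.** Table 5.19 tests oxygen use in all infants, and Table 5.21 prints N per arm. That helps interpretation but does not make the Table 5.21 test a randomised comparison.

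**Scoring every non-user as 21% would reward early death.** The protocol expects 14.6% mortality. An infant who dies before receiving oxygen or ventilation would get the best possible score. This is right, and the fix must deal with it.

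**Conclusion.** The point holds as a matter of definition. Followed as worded, Table 5.21 compares subsets selected after randomisation under an intention-to-treat label. Whether this happens in practice depends on a coding rule that the SAP does not give.

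The size depends on oxygen use, which the documents do not report. If the intervention only spares mild infants oxygen, wrong-direction significance is about 6 to 9% when use is 90% or more in both arms with differences of 3 to 5 points. It is about 25% at 90 vs 80%, and higher only at lower use. If the intervention lowers need in all infants, the cost is power and not direction.

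A reader might extend the criticism to the durations of oxygen, invasive and non-invasive ventilation, and iNO. The documents do not support calling those biased: 0 days is a natural entry for a non-user, and nothing says that non-users are missing. That part is a request for confirmation. The primary analysis is unaffected.

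**What to change.** In SAP 4.1.2, define the variable as highest FiO2 in the NICU for all intention-to-treat infants, and score those never given supplemental oxygen as 21%. In SAP 4.3, reserve the missing row for data not recorded. Label any users-only summary as descriptive.

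State a separate rule for infants who die before receiving oxygen or respiratory support. They should not be scored as 21% or 0 days. Either rank them worst in the Wilcoxon test, or report them separately with a sensitivity analysis.

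Confirm in one sentence that surviving non-users enter the four duration variables as 0 days.

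The cost is a few lines of text and a recode before database lock, with no new data collection. The downsides are ties at 21% and at 0 days, which the Wilcoxon test handles, and the need to justify the rule for early deaths. The recode removes the spurious wrong-direction result but does not make the test sensitive to pure sparing: in that model the all-infants test was significant in only 5%, 10% and 23% of trials at 90 vs 80%, 80 vs 65% and 70 vs 50% use. Table 5.19 remains the direct test of oxygen use.
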